## 8. Background Information and Scientific Rationale

The COVID-19 pandemic started in China in December 2019 and spread to European countries in early 2020, affecting most severely Italy, Spain and France. Belgium was affected during the same wave and first deaths due to COVID-19 were reported in early March 2020. As of September 10, 2020, almost 28 million cases, including 900,000 deaths, have been confirmed over the world and almost 90,000 cases, including 9,900 deaths, have been declared in Belgium [10].

Current data from the Belgian surveillance system indicate that 20% of the hospitalized patients are in ICUs [11]. Hospital deaths occur either in the ICU (13 / 31, 31 % in Liège University Hospital, personal data) or in non-ICU wards for those patients who would not benefit from intensive care as anticipated by the medical team [12]. Based on United Kingdom ICNARC reports, and according to personal observations in Belgium, the COVID-19 ICU patients require mechanical ventilation in 60% of cases, particularly when they are referred directly by the emergency medical service. According to different series, forty to sixty percent of the mechanically ventilated patients are likely to die, most of them when mechanical ventilation is instituted early (30% survival rate) rather than late in the course of the disease (70 % survival rate) [13]. Similar observations have been made in China [14]. Besides the direct cost in human lives, the current situation in European countries has led to a halt in most of medical and scheduled surgical practices for non COVID-19 patients and to a doubling of the number of ICU beds. The nursing and medical manpower per patient in ICUs has also been doubled due to the intensity of care that patients require with the use of invasive ventilation and the practice of alternate prone positioning for severe ARDS [15].

Several epidemiologic projections suggest that, in the absence of an effective antiviral vaccine or of therapeutic agents, the human cost may reach as many as 45 million deaths until the global population has developed self-immunization. Preliminary data suggest that immunization occurs within 15 to 20 days of illness in most patients [16] but data in the community are still lacking. The potential duration of the current pandemic is largely unknown and epidemics with coronaviruses are likely to recur. A race for developing active therapies and vaccines started since the onset of the pandemic [16]. The potential therapeutic agents are directed against either the virus itself or the mediators of the exacerbated host response observed in the most severe cases [17]. Current proposed treatments are under evaluation and new therapies and vaccines directed against SARS-CoV-2 are at preliminary steps of development [18]. Therapy with plasma collected from convalescent patients has been proposed to provide passive immunization to the patients at risk of developing severe COVID-19 in small pilot uncontrolled studies [19,20].

Convalescent plasma therapy also called immune plasma therapy has been used to prevent or treat numerous viral diseases for over a century. Besides historical records in rabies, polio, measles, hepatitis or influenza, convalescent plasma therapy has been used successfully against Ebola and during the two previous coronavirus epidemics: SARS-CoV in 2002 and MERS. In a retrospective study, Cheng et al. report that amongst the 339 patients admitted for SARS at the Prince of Wales hospital in Hong-Kong, 80 received convalescent plasma. Mortality in this group was 12.5% and considered lower than the mortality rate of SARS in Hong-Kong (17%) [21]. Interestingly, patients with a good outcome received plasma at day  $11.7 \pm 2.3$  vs  $16.0 \pm 6.0$  in the other ones. The volume administered was 250 to 300 mL and no adverse effects were observed. A meta-analysis published in 2015 on 27 publications describing the effect of convalescent plasma in severe acute respiratory infections of viral origin (including SARS-CoV, H1N1 and H5N1 influenza) similarly reported an overall reduction of mortality (OR 0.25 (0.14-0.45) and no adverse effect [22].

In COVID-19, Shen et al. recently reported 5 patients under mechanical ventilation who received 400 ml convalescent plasma between 10 and 22 days after admission. SOFA scores were 5, 10, 3, 3 and 2, respectively. Bacterial infection was documented in two of them. All of them were treated with lopinavir/ritonavir and IFN- $\beta$ 1. ARDS resolved in four patients and 3 of them could be weaned from mechanical ventilation at the time of publication [19]. Duan et al. reported 10 cases of patients with severe infection receiving convalescent plasma between 11 and 20 days after the onset of symptoms. Prior to treatment, three patients received mechanical ventilation, three received high-flow nasal cannula oxygenation, and two received conventional low-flow nasal cannula oxygenation. Three patients were discharged and the seven others improved and were ready to discharge at the time of publication [20]. In all the published cases of COVID-19 patients, convalescent plasma was associated with a reduction of viral load despite all the patients were receiving various antivirals (including lopinavir/ritonavir or remdesivir). In the study by Shen et al, the Ct value increased in all patients at day 1 post transfusion up to 40 in all patients at day 12 [19]. Duan et al. observed that 10/10 patients reached undetectability 2 to 6 days after the administration of convalescent plasma [20]. A direct antiviral effect of neutralizing antibodies within the convalescent plasma is therefore likely to play a central role in the beneficial effect of the treatment. Nevertheless, it cannot be ruled out that other mechanisms could participate in the effect. It is well known that IV immunoglobulins have a potent anti-inflammatory effect by various mechanisms including engagement of inhibitory Fc $\gamma$ R on macrophages and regulatory T cells [23]. Although the amount of IgG present in two units of plasma is clearly lower than the dose of IgG administered during IVIG therapy, such an effect could take place during treatment with convalescent plasma. Other mechanisms could also intervene. Abnormalities of coagulation and complement activation have been described in Covid [24] and are clearly amenable to improvement after plasma administration. In addition, inhibition of ACE2 enzymatic activity by viral infection has been proposed as a central mechanism in the pathogenesis of COVID-19 [25]. Since ACE2 catalytic activity can be

demonstrated in the plasma due to shedding of the ectoenzyme [26], a beneficial antibody-independent effect of plasma therapy cannot be excluded.

Besides rare adverse effects associated with plasma therapy in general, including transfusion- related acute lung injury (TRALI) [27], convalescent plasma therapy raises the issue of potential *antibody dependent enhancement* (ADE). ADE is the paradoxical exacerbation of an infectious disease due to the appearance of specific antibodies produced by the infected subject. It has been observed in several viral diseases including Dengue, Ebola, HIV, Sars CoV and MERS CoV. In coronavirus infections, the main mechanism involves a facilitation of virus entry in FcγR expressing cells by antibodies directed against the spike protein but with a suboptimal neutralizing affinity [28]. Observations in dengue also suggest that sub-neutralizing antiviral antibodies could also contribute to inhibit IFN-γ secretion and cytotoxic T cell differentiation [29]. Although ADE clearly plays an important role in the pathogenesis of viral infections, it is important to state that it has never been observed after convalescent plasma therapy. In the Shen's study [19], the donors had been asymptomatic for at least 10 days and had a neutralizing antibody titer higher than 1/40. No precision is given regarding the severity of their symptoms. In the study by Duan et al [20], 40 donors were included. The donor's blood was collected after 3 weeks of illness and 4 days of hospital discharge. 39 donors had a neutralizing antibody titer higher than 1/160. In a most recent survey, Joyner observed 2 serious adverse events directly related to convalescent plasma administration for COVID-19 in a cohort of 5,000 patients (0.04 %) treated in the USA [30]. In a series of 175 patients with mild COVID-19 from Shangaï, China, Wu et al [31] observed that the titers of neutralizing antibodies assessed at hospital discharge to SARS-CoV-2 varied substantially. In 11 patients with sequential assessments, high titers over 1/256 were measured as early as 10 to 16 days of disease onset.

### Hypothesis

Our hypothesis is that passive immunization with plasma collected from patients having contracted COVID-19 and developed specific antibodies may alleviate symptoms and viral load of SARS-CoV-2 and reduce mortality in patients treated with mechanical ventilation for severe respiratory failure during the evolution of SARS-CoV-2 pneumonia as compared with standard of care. Considering the high number of current trials testing therapies against COVID-19, we anticipate that we may have to adapt the standard of care depending on the evolution of guidelines.

### Current trials testing convalescent plasma therapy in COVID-19 patients

As of April 25, 2020, 41 randomized trials testing the use of convalescent plasma in COVID-19 patients have been declared on Clinicaltrials.gov. Four of these include critically ill patients. NCT 04362176 (Vanderbilt, Nashville, TN, USA) plans to include 500 patients and compare (1:1) convalescent plasma

to placebo (Ringer Lactate), NCT04359810 (Columbia, New-York City, NY, USA) plans to include 105 patients and compare (2:1) 1 unit of convalescent plasma to 1 unit of fresh frozen plasma. NCT 04346446 (New Dehli, India) is open label and plans to include 20 patients. NCT04381858 (Mexico) plans to include 500 patients and compare convalescent plasma vs human immunoglobulin. As of August 28, 63 RCT have been posted on Clinicaltrials.gov. Eighteen trials plan to enroll at least 300 patients. None of them addresses specifically mechanical ventilated patients.

## 9. Investigational plan

### 9.1. Design

- Inclusion and randomization

After fulfilling the inclusion criteria, patients will be included by the local investigator in each participating center and randomized through a standard randomization system (UCL clinical trial center, Pr [name]) into 2 arms (1:1) to receive 2 units (400-500 mL in total) of convalescent plasma plus standard of care from 2 different donors preferably (intervention group) or control treatment made of standard of care alone.

### 9.2. Description of population

- The study population will be patients with SARS-CoV-2 pneumonia associated with acute respiratory failure and requiring mechanical ventilation
- Number of patients planned: 500 (1 intervention group of 250; 1 control group of 250)

### 9.3. Participants eligibility

#### 9.3.1 Inclusion criteria

We will include patients with the following criteria:

- age at least 18 years
- hospitalization in an intensive care unit participating to the study
- medical diagnosis with SARS-CoV-2 pneumonia as defined by both:
  - o extended interstitial pneumonia on CT scan or a chest X-ray, consistent with viral pneumonia, within 10 days prior to inclusion
  - o Positive result of SARS-CoV-2 PCR test, or any emerging and validated diagnostic laboratory test for COVID-19, within 15 days prior to inclusion
- under mechanical ventilation administered through an endotracheal tube, for no more than 5 days
- prior Clinical Frailty Scale < 6 [32] (see appendix F ).
- written consent of the patient, or – if impossible - of a relative acting as the legal representative, or – if impossible - of a physician from a non-participating department of the same hospital acting as an impartial witness (see trial procedures).

#### 9.3.2 Exclusion criteria

- Pregnancy
- Prior episode of transfusion-related side effect
- Medical decision to limit therapy

- Current participation in another trial testing a COVID-19 therapy

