## 7. Objectives

### 7.1. Primary

The principal objective of the CONFIDENT trial is to assess the efficacy of 2 units (400-500mL) of plasma collected in convalescents of COVID-19 infection with a titer greater or equal to 1/320 (plaque reduction neutralization test 50) neutralizing antibodies against SARS-CoV-2 with the standard of care, as compared to standard of care, to reduce the mortality at day 28 after inclusion of the patients with SARS-CoV-2 pneumonia who require mechanical ventilation. In case of shortage of plasma with a titer greater or equal to 1/320 on the moment of patient enrolment, plasma from convalescent donors with a titer of at least 1/80 will be released for transfusion. The standard of care will be made of therapies currently recommended in international guidelines regarding organ failure support and treatment of secondary events. At the present time, no treatment is directed against SARS-CoV-2 or the inflammatory response characteristic of this specific disease. In case of evolution of the guidelines due to new scientific release during the study period, the standard of care will be adapted in the two treatment groups.

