3 separate units (e.g. 3x200 ml). Final products will be specifically labelled as COVID-19 Convalescent Plasma and stored in a dedicated location. The processing that is routinely used for pathogen reduction by Methylene Blue will be applied according to standard practice in the blood establishment.

The production process and product characteristics will comply with current Belgian Blood legislation. For this trial, volumes will be between 200 and 250 ml. The product can be stored for 36 months at a temperature below -25°C or for 3 months at a temperature between -18°C and -25°C.

Data collected from donors

The following data will be collected:

- Date of nasopharyngeal swab that subsequently proved SARS-CoV-2-positive by PCR (or alternative date of radiological confirmation)
- Time from diagnosis until resolution of symptoms

Testing of donated plasma

Defined SARS-CoV-2 neutralizing antibody titers will be measured in the donated plasma. A Blood or Plasma sample from all donors will be stored in tube with gel for that purpose and for testing of antibody specificities.

Blood establishments will determine SARS-CoV-2 neutralizing antibody titers at or prior to the first donation to allow the selection of donors with high titers. The neutralizing antibody titers will be repeated with a maximal interval of one month. Samples of donations done in-between will be stored for later testing.

The Blood Establishment will qualify donations from donors with neutralizing antibody titers greater or equal to 1/320 as appropriate for this study. In case of shortage of plasma with a titer greater or equal to 1/320 on the moment of patient enrolment, plasma from convalescent donors with a titer of at least 1/80 will be released for transfusion.

If an adequate correlation between neutralizing activity and Elisa antibody testing for SARS-CoV2 were to be demonstrated by a validation report to be approved by the sponsor, this assay could replace the test for neutralizing antibodies. Additional archive samples of the donated plasma will be saved for reference studies e.g. frozen aliquots from plasma samples taken at the time of donation.

When the measured neutralizing activity in the collected plasma is considered too low, the plasma will be made available for other use.

Convalescent Plasma and Dosing Regimen

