#### **9.4.2 Identity of Investigational Product (s)**

Intervention arm: 2 units (400-500 mL in total) of convalescent plasma. The treatment will be administered within 24 hours of inclusion in the study, through a venous line over at least 2 hours. (to prevent potential adverse effect of fluid overload).

Control arm: no plasma

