#### **9.4.5 Prior and concomitant therapy**

At the present time, no specific treatment has been proven to improve the outcome of COVID-19 critically ill patients beside the conventional support of organ failure. The treatments administered in compassionate use on a frequent basis (*i.e.* hydroxychloroquine or azithromycin) or on selected cases (*i.e.* anti-HIV or Ebola antivirals, anti-cytokines or anti-cytokine receptors ...) are likely to be dispatched similarly in the randomization arms and can be used in the patients included in this trial. Their use will be assessed and provided in the descriptive results of the population.

No particular drug-drug interactions are anticipated.

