### **9.5.4 Visits**

#### **9.5.4.1 Screening**

The principal investigator of each participating center will organize the detection of potentially eligible patients, based on medical history and inclusion criteria available in the patient's record, gather consent to participate according to the study protocol. The response must be yes to all the following questions:

[figure not shown]

- Age > 18 years
- Hospitalisation in a ICU participating to the study
- extended interstitial pneumonia on CT scan or chest X-ray, consistent with viral pneumonia, within 10 days prior to inclusion
- Positive result of SARS-CoV-2 PCR test, or any emerging and validated diagnostic laboratory test for COVID-19, within 15 days prior to inclusion
- Under mechanical ventilation administered through an endotracheal tube, for no more than 5 days
- prior Clinical Frailty Scale < 6
- written consent of the patient, or – if impossible - of a relative acting as the legal representative, or – if impossible - of a physician from a non-participating department of the same hospital acting as an impartial witness (see trial procedures)
- No pregnancy
- No prior episode of transfusion-related side effect
- No medical decision to limit therapy
- No current participation in another trial testing a COVID-19 therapy

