#### **9.5.14 Premature discontinuation of trial treatment**

The treatment will be delivered as a single administration of convalescent plasma. In case of severe adverse reaction during the administration (specifically hemodynamic shock), the study plasma will be stopped, and the adverse event described and collected.

If for any reason the treatment is either not administered or prematurely stopped, the patient will remain in the trial for the intention to treat analysis.

No cross-over will be allowed.

| Procedures*                          | Visits    |           |                 |      |      |      |               |     |      |
|--------------------------------------|-----------|-----------|-----------------|------|------|------|---------------|-----|------|
|                                      | Screening | Inclusion | Treatment Phase |      |      |      | Follow Up     |     |      |
|                                      |           | D1        | D7              | D14  | D21  | D28  | ICU Discharge | D90 | D365 |
| Informed consent                     |           | x         |                 |      |      |      |               |     |      |
| Eligibility assessment               | x         | x         |                 |      |      |      |               |     |      |
| Randomisation                        |           | x         |                 |      |      |      |               |     |      |
| Medical history                      |           |           |                 |      |      |      |               |     |      |
| Comorbidities                        |           | x         |                 |      |      |      |               |     |      |
| Prior medications                    |           |           |                 |      |      |      |               |     |      |
| APACH II score                       |           | x         |                 |      |      |      |               |     |      |
| SOFA score                           |           | x         | x               | x    | x    | x    |               |     |      |
| WHO disease progression scale        |           | x         | x               |      |      |      | x             |     |      |
| CRP                                  |           |           |                 |      |      |      |               |     |      |

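### Earlier convalescent plasma or other anti-SARS-CoV-2 antibody treatment is not an exclusion, so already-treated patients could enter the "no plasma" arm and dilute the comparison (minor)

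*Protocol*

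**What the plan says.** Section 9.3.2 of the protocol has four exclusions: pregnancy, an earlier transfusion-related side effect, a decision to limit therapy, and "Current participation in another trial testing a COVID-19 therapy". The screening checklist in 9.5.4.1 turns the last into "No current participation in another trial testing a COVID-19 therapy" and adds nothing on earlier treatment. The inclusion criteria in 9.3.1 do not mention it either.

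The contrast is plasma plus standard of care against standard of care alone (7.1, 9.1). Section 9.4.2 describes the comparator as "Control arm: no plasma".

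Three other statements bear on the point:

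- Section 9.4.5 says that treatments in compassionate use "are likely to be dispatched similarly in the randomization arms and can be used in the patients included in this trial".
- Section 7.1 says that, if guidelines change, "the standard of care will be adapted in the two treatment groups".
- Section 9.5.14 says "No cross-over will be allowed", under premature discontinuation of the trial treatment.

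**The concern.** Eligibility should protect the contrast that the trial tests. A patient who received plasma or another anti-SARS-CoV-2 antibody product before intubation has already had the experimental treatment or something close to it. In the control arm that patient is analysed as untreated. In the plasma arm the trial units may add little.

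No existing rule closes the gap. The trial-participation exclusion covers only current participation, so treatment outside a trial, or in a trial that the patient has left, does not exclude. The cross-over ban concerns what happens after randomisation. Section 9.4.5 relies on balance between arms. Balance prevents confounding, but it does not prevent dilution when the earlier treatment is the intervention itself.

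Two things are at stake: the size of the day-28 mortality difference, and the reading of sero-positivity at days 1, 7, 28 and 90 (7.3). Antibody transfused before inclusion can make a patient positive at day 1 without any response of the patient's own, which also bears on the sero-conversion objective (7.2).

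**Working it through.** **Inputs from the protocol**

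- Control day-28 mortality 40%; relative reduction one third, so plasma mortality 0.40 × 2/3 = 26.7% (9.9).
- 250 patients per arm, two-sided α 5%, β 20% (9.9).
- Looks at 100, 200, 300, 400 and 500 patients. Efficacy P limits in Table 2: none, 0.001, 0.007, 0.022, 0.042 (9.9).
- The synopsis gives a different effect: a 30% relative reduction, so 40% versus 28%.

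**Reproducing the plan's own figure**

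The usual two-proportion formula (pooled variance, no continuity correction) for 40% versus 28% gives 244 per arm, 488 in total, within 3% of the stated 500. Power at 250 per arm is 81%. For 40% versus 26.7% the formula gives 196 per arm and power 89% at 250. Simulating the sequential design with the Table 2 efficacy limits, at least 200,000 trials per case, gives 80% and 88% respectively.

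**Dilution model (assumed)**

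Let f be the share of patients in both arms who had an earlier antibody product, and D = 40 − 26.7 = 13.3 points.

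- Full earlier effect, nothing added by trial plasma: control mortality = (1 − f) × 40% + f × 26.7%, plasma mortality 26.7%, difference = (1 − f) × D. Example at f = 10%: 36.0 + 2.67 = 38.7%, and 38.7 − 26.7 = 12.0 points.
- Half the effect in controls, plasma arm still at 26.7%: difference = (1 − f/2) × D. Example at f = 10%: 0.95 × 13.3 = 12.7 points.

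**Power, 40% versus 26.7%, Table 2 efficacy limits, futility limits ignored because they are non-binding**

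| f | Difference, full effect | Power, full effect | Power, half effect |
|---|---|---|---|
| 0 | 13.3 | 88% | 88% |
| 1–2% | 13.2–13.1 | about 87% | – |
| 5% | 12.7 | 85% | about 86% |
| 10% | 12.0 | 80–81% | about 85% |
| 20% | 10.7 | 71% | about 81% |

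**With the synopsis effect (40% versus 28%), full earlier effect**

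Power is 80%, 76%, 72% and 62% at f = 0, 5, 10 and 20%. There is no slack here, because the starting value is already at the planned 80%.

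**Type I error**

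If plasma has no effect, earlier plasma changes nothing and both arms have the same mortality whatever f is. The simulated chance of a false claim of benefit is 2.5% with 40% mortality in both arms, as intended for a two-sided 5% test.

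**The case against.** The strongest case against is that the group may hardly exist. Eligibility requires a positive test within 15 days and at most 5 days of ventilation (9.3.1). A patient who received plasma in a ward trial that recently would usually still be in follow-up, and so barred as a current participant. That stands, and it removes most of the obvious source.

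A reader might infer from other passages that plasma is being given to COVID-19 patients outside trials. The text does not support this. Section 9.4.1 says that when the neutralizing activity is too low "the plasma will be made available for other use", without saying that the use is transfusion to COVID-19 patients. Section 9.5.5 lists data to be shared at European level; it does not report off-trial use at the participating centres. The examples in 9.4.5 include no plasma or antibody product. The 63 trials mentioned in section 8 are a registry total, and no Belgian ward trial is described.

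A second objection is that patients who were intubated despite earlier plasma are selected for its failure, so the dilution in controls may be small. This holds as far as trial plasma would still help them. If neither the earlier product nor the trial units help such patients, the difference shrinks by the same factor (1 − f).

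Third, the protocol records recent immunotherapy (9.5.4.2), day-1 total and neutralizing antibodies (9.5.4.2) and concomitant drugs against SARS-CoV-2 (visit table in 9.5.14). These could identify some of the patients and limit the damage to the sero-positivity endpoint. None is a condition of eligibility, and none asks about earlier plasma by name.

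Finally, broad eligibility is a legitimate pragmatic choice. That is a fair reason to call the point minor, but the proposed exclusion costs that aim very little.

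**Conclusion.** The gap is real and small. Nothing in the eligibility rules keeps out a patient who already received convalescent plasma or another anti-SARS-CoV-2 antibody product in the current episode, and such a patient could be analysed in the no-plasma arm. The consequence is dilution towards no difference if earlier plasma works, and a less clear sero-positivity endpoint.

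A reader might go further and infer that the comparison is biased between arms or that false positives become more likely. Neither follows: randomisation spreads these patients over both arms, and under no effect the arms remain equal.

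Nor do the documents support saying that the trial will lose material power. The share f is unknown. At 1–2% the loss is about one point. Under the one-third reduction in 9.9, power stays at or just above 80% up to a share of about 10% even with full earlier effect, and at about 81% with half the effect at 20%. Only a share near 20% with full effect takes it down to 71%. Under the smaller synopsis effect any share takes power below 80%. If the futility limits are followed as well, power starts at about 78% before any earlier plasma is considered. That starting shortfall belongs to the futility rule and not to this point.

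Severity: minor.

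**What to change.** Add one exclusion to section 9.3.2, and the matching question to the checklist in 9.5.4.1: *receipt of convalescent plasma or any other anti-SARS-CoV-2 antibody product during the current COVID-19 episode*.

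The cost is one line in an amendment and one more screening question. A few screened patients become ineligible. The sample size, the interim limits and the conduct of treatment are unaffected.
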